#### Outcomes

##### System Usability Scale

The scale was created in 1986 by Brooke [41] to measure the usability of products and services, including hardware, software, mobile devices, websites, and applications. It consists of a 10-item questionnaire with five response options for respondents that range from *strongly agree* to *strongly disagree* [41]. This scale will be used to assess the usability of the app.

#### Primary Outcome

##### Discretionary Salt Questionnaire

The discretionary salt questionnaire was validated in a previous study [42,43] on the Brazilian population. Participants will report their regular monthly salt consumption (number of 1 kg packages of salt consumed per month), the number of persons who ate meals at home, the age of each person, and the number of meals that each person eats per week at home to correct the salt consumption per person. Children younger than 3 years will not be considered in the calculation, and the meals of children younger than 10 years will be regarded as half meals. The following steps will be used to calculate the salt intake per person: divide the amount of salt (grams) used per month at home by 30 and multiply the quotient by 7 (=grams of weekly salt intake at home), divide this amount of weekly salt intake by the total number of weekly meals (=grams of salt intake/meal), multiply the amount of salt used per meal by the number of meals eaten per week by the participant, and divide the total weekly salt intake of the participant by 7, resulting in the estimated quantity of individual daily added salt. The discretionary salt questionnaire will be used to evaluate the efficacy of the intervention.

#### Secondary Outcomes

##### Habit

The first psychosocial variable interferes with the adoption of behavior and will be evaluated through the mean of 10 items [44] assessed on a 5-point scale (1, definitely not, to 5, definitely yes). The guiding phrase for the investigation of the habit will be “Using more than one level teaspoon of salt/day (ie, more than 3 g of salt) during cooking is something that I do...” The items will be “I do it frequently”; “I do it automatically”; “I do it without having to remember to do it consciously”; “If I don’t, it make me feel strange”; “I do it without thinking”; “It would take effort not to do it”; “It is part of my day-to-day”; “I start doing it without realizing that I’m already doing it”; “I would find it difficult not to do”; and “I've been used to doing this for a long time.” The higher the response score, the greater the individual’s favorability of not restricting the amount of salt used during cooking.

##### Self-Efficacy

The second psychosocial variable will be estimated through the mean of 5 items [44] rated on a 5-point scale (1, completely disagree, 5, completely agree. The higher the score, the greater the perception of self-efficacy to perform the behavior. The statements were “I trust my ability to use 1 level teaspoon of salt a day during cooking,” “I can use 1 level teaspoon of salt a day during cooking,” and “I am sure that I can use 1 level teaspoon of salt a day during cooking.”

##### Intention

The last psychosocial variable will be estimated through the mean of 6 items [44] rated on a 5-point scale. A high score indicates a high intention to perform the behavior. “I am planning to use 1 level teaspoon of salt a day during cooking” (1, definitely not, 5 definitely yes), “I will try to use 1 level teaspoon of salt a day during cooking” (1, definitely not, 5, definitely yes), “I want to use 1 level teaspoon of salt a day during cooking” (1, I totally disagree, 5, I totally agree). “I hope to use 1 level teaspoon of salt a day during cooking” (1, unlikely, 5, very likely), “How likely are you to use 1 level teaspoon of salt a day during cooking” (1, unlikely, 5, very likely).

#### Data Collection

Data collection will be performed in three steps (T0, T1, and T2), considering a period of 1 month between them. At the first step (T0), participants will be informed about the research, the study’s relevance, and the need to return to the next meeting, and will sign the informed consent form. Sociodemographic data, the discretionary salt questionnaire, habit, self-efficacy, and intention will be evaluated; the mobile app will be installed on their phone and guidance will be given on using the mobile app. Both groups will be assessed at T1 (1 month after T0) and T2 (1 month after T1) for the discretionary salt questionnaire, habit, self-efficacy, and intention variables. The usability of the mobile app (System Usability Scale) will be evaluated in the intervention group in T1 and T2. At the end of the study, participants in the CG will have the right to have the app installed on their cell phones if they wish and receive instructions on how to use it.

#### Data Analysis

Qualitative data will be described using frequencies and percentages, and quantitative data as measures of central tendency (mean and median) and dispersion (SD, maximum, and minimum). Correlation tests (Spearman or Pearson coefficient) will test the relation between habit and self-efficacy with intention at T0. Regression analysis using generalized linear models will be used to verify if habit, self-efficacy, and intention at T0 predict the discretionary salt questionnaire at T1 and T2.

To evaluate the efficacy of the intervention, comparisons between groups and times about the discretionary salt questionnaire will be performed using a linear regression model via generalized estimating equations modeling [45].

A significance level of 5% will be adopted. Statistical analyses will be performed using SAS, version 9.4 (SAS Institute).

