#### Sample Size and Recruitment

According to the quantitative outcomes, the sample size was calculated considering the objective of comparing the two groups (control group [CG] and intervention group [IG]) in the three periods of time. The methodology of a sample calculation for a repeated-measures ANOVA model was considered to perform this calculation. In this calculation, a significance level of 5%, a test power of 80%, and an effect size of 0.25 were assumed, which, according to Cohen [39], can be considered a medium degree effect size. The first calculation resulted in a sample of 86 participants, but a 20% rate for possible losses was considered, which resulted in a sample of 108 participants (54 participants per group).

Recruitment will occur in primary health care centers of a Brazilian town, with the help of the community health agent of the unit that is linked to each resident of its microarea; the individual will be approached and will invite a resident at home who meets the inclusion criteria to participate in the study. Participants will be selected in a randomized way and will be divided between groups (IG and CG), considering a randomization scheme by blocks of random size. The randomization scheme was generated online [40].

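### The efficacy GEE names no adjustment for T0 salt, which is collected from everyone; adjusting would make the primary comparison more precise, by about a quarter to a third of the variance if the between-visit correlation is near 0.5

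*Protocol article*

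**What the plan says.** The protocol article, Module 3, Data Analysis, has one sentence on efficacy: "comparisons between groups and times about the discretionary salt questionnaire will be performed using a linear regression model via generalized estimating equations modeling". It names no covariate, no primary contrast and no working correlation, and it does not say whether T0 salt is an outcome row or a predictor.

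Two other sections bear on how T0 enters:

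- Data Collection lists the T0 measurements: "Sociodemographic data, the discretionary salt questionnaire, habit, self-efficacy, and intention will be evaluated". For follow-up it says "Both groups will be assessed at T1 (1 month after T0) and T2 (1 month after T1) for the discretionary salt questionnaire". The primary outcome is therefore available at all three visits in both arms.
- Sample Size and Recruitment gives the objective as "comparing the two groups (control group [CG] and intervention group [IG]) in the three periods of time". It adds that "The methodology of a sample calculation for a repeated-measures ANOVA model was considered to perform this calculation", with "a significance level of 5%, a test power of 80%, and an effect size of 0.25 were assumed".

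The same Data Analysis section does name T0 predictors for a different set of regressions, in which habit, self-efficacy and intention at T0 predict later salt. T0 salt is not among them, and those models are not the efficacy analysis.

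**The concern.** Read together, these sections treat T0 as one of the outcome times. In a standard group-by-time parameterisation there are then two natural effect estimates. One is the difference between arms at T1 or T2, which ignores T0. The other is the difference in change from T0, which subtracts T0 with full weight whatever the correlation. Adjusting for T0 salt weights it by the observed correlation and is more precise than either.

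The outcome gives some reason to expect T0 to be informative. Household salt is allocated using "the number of persons who ate meals at home, the age of each person, and the number of meals that each person eats per week", and household composition may well change little in two months. That stability is plausible, but the article does not document it.

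At stake are the width of the interval for the app effect and the power of a small trial. In any one trial, a chance imbalance in T0 salt also carries through to the raw comparison in proportion to the correlation, and is over-corrected by the change score.

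**Working it through.** **1. The plan's own sample size.** Inputs from Sample Size and Recruitment: f = 0.25, two-sided F test at 5%, power 80%, m = 3 measurements, 2 groups. For the between-groups test in a repeated-measures ANOVA, the noncentrality is λ = N·f²·m / [1 + (m − 1)ρ], with 1 and N − 2 degrees of freedom. The correlation ρ is not in the article. At ρ = 0.5 and N = 86, λ = 86 × 0.0625 × 3 / 2 = 8.06 and power is 0.801. N = 86 is therefore reproduced, matching "The first calculation resulted in a sample of 86 participants". With ρ = 0.3 the same formula gives N = 70, and with ρ = 0.7 it gives N = 104. The group-by-time interaction variants give 28 (at ρ = 0.5) or 156, not 86. Allowing for 20% losses, 43 / 0.8 = 53.75, or 54 per arm and 108 in total, as stated. So ρ = 0.5 is the value consistent with the stated size, but it is an inference from that size.

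**2. Assumptions for the precision check.** Equal SD σ at each visit; compound symmetry with correlation ρ; 43 completers per arm; a true difference of 0.5σ at T1 and T2 (f = 0.25 for two groups corresponds to d = 2f = 0.5); two-sided 5% noncentral-t power.

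**3. Per-person variance, in units of σ².**

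- Mean of T1 and T2: raw (1 + ρ)/2; change from T0 (1 + ρ)/2 + 1 − 2ρ = 1.5(1 − ρ); T0-adjusted (1 + ρ)/2 − ρ².
- T2 alone: raw 1; change 2(1 − ρ); T0-adjusted 1 − ρ².

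**4. Results: variance, with power in brackets.**

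| Contrast | ρ | Raw | Change | T0-adjusted | Cut vs raw | Cut vs change |
|---|---|---|---|---|---|---|
| Mean T1, T2 | 0.3 | 0.65 (81%) | 1.05 (61%) | 0.56 (86.5%) | 14% | 47% |
| Mean T1, T2 | 0.5 | 0.75 (75%) | 0.75 (75%) | 0.50 (90%) | 33% | 33% |
| Mean T1, T2 | 0.7 | 0.85 (70%) | 0.45 (93%) | 0.36 (97%) | 58% | 20% |
| T2 alone | 0.3 | 1.00 (63%) | 1.40 (49%) | 0.91 (67%) | 9% | 35% |
| T2 alone | 0.5 | 1.00 (63%) | 1.00 (63%) | 0.75 (75%) | 25% | 25% |
| T2 alone | 0.7 | 1.00 (63%) | 0.60 (84%) | 0.51 (89%) | 49% | 15% |

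For the mean of T1 and T2 at ρ = 0.5, the standard error √(2 × variance / 43) falls from 0.187σ to 0.153σ, or 18%. The variance ratio 0.75 / 0.50 = 1.5 is equivalent to 50% more participants.

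**5. Check by simulation.** The formulas treat the T0 slope as known. A simulation of 4,000 replicates with 43 per arm, in which the slope was estimated, gave these reductions against the change contrast: 45%, 34% and 20% for the mean of T1 and T2 at ρ = 0.3, 0.5 and 0.7; and 33%, 26% and 15% for T2. These agree with the table.

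**The case against.** **The article is silent rather than wrong.** It is condensed, and covariates are often left to a fuller plan. This stands in part. A reader might infer that the authors decided against baseline adjustment, but the article does not say so. It also never states outright that T0 is an outcome row; the phrase about three periods belongs to the sample-size objective. Still, the article states a model and its comparison factors, and it names T0 predictors for its other regressions. The description as it stands points to a model without T0 adjustment, and the point is fair on that footing.

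**A three-time GEE need not lose anything.** If the T0 means are constrained equal across arms, as randomisation justifies, and a suitable working correlation is used, essentially all of the gain is recovered. That model would fit the article's wording. This stands, and it is why the constrained form is offered as an equal remedy. Nothing in the article indicates the constraint.

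**The size of the gain is assumed.** The article gives neither ρ nor an SD. The outcome rests on a self-reported count of 1 kg packages per month, which is coarse and may correlate only modestly between visits. This stands. A reader might take one third as a property of this trial, but it holds only for the mean of T1 and T2 with ρ near 0.5. In some cells the gain in power is small: 81% to 86.5% against raw at ρ = 0.3, and 93% to 97% against change at ρ = 0.7, both for the mean.

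**Moving T0 out of the outcomes has a cost.** The covariate form no longer estimates change from T0 within each arm, which is part of a comparison between times. This also stands, and is dealt with under the fix.

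**Conclusion.** The point holds as one of efficiency. The efficacy model as described names no adjustment for a baseline value of the primary outcome that is collected in both arms, and adjusting would be more precise than either the raw or the change contrast at every ρ examined. Under compound symmetry and equal SDs, the variance reduction at ρ = 0.5 is 33% for the mean of T1 and T2 and 25% for T2 alone. It runs from about 9% to 58% over ρ of 0.3 to 0.7, depending on the contrast. The article supplies no ρ; the only anchor for 0.5 is that it reproduces the 86.

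Two stronger readings are not supported. First, a reader might infer that the planned analysis is biased or invalid. It is not: under randomisation the raw and change contrasts are both unbiased, with valid intervals. Second, because 86 reproduces as a between-groups test over three measurements, a reader might infer that the test will be a group effect pooled over T0, T1 and T2. That would dilute a 0.5 SD effect to 0.5 × 2/3 = 0.33 SD and give about 46% power at ρ = 0.5. The article does not say that this term carries the efficacy test, and its analysis sentence refers to groups and times, so this cannot be charged to the plan.

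The change is worth making, but the trial does not fail without it.

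**What to change.** Replace the efficacy sentence in Data Analysis with wording such as: *Discretionary salt at T1 and T2 will be analysed with a linear GEE with arm, visit, arm-by-visit, T0 discretionary salt and T0-by-visit as covariates; the efficacy estimate is the adjusted difference between IG and CG.* State whether the primary contrast is the difference at T2 or the average over T1 and T2. The arm-by-visit term lets the effect differ between the two visits, so that a common effect is not imposed.

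Alternatively, keep all three times in a group-by-time GEE, constrain the T0 means to be equal across arms, and specify an exchangeable or unstructured working correlation.

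The cost is a sentence or two of analysis text, with no new data and no additional participants. The one small downside is that the covariate form does not estimate within-arm change from T0. That change can be reported descriptively or taken from the constrained form. The amendment should be dated and made before outcome data are compared by arm.

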### Ethics and Dissemination

Participants from the data collection of phases 1 of module 2 (user needs assessment) and module 3 (implementation and evaluation of intervention) will provide written informed consent. At this moment, complete and adequate information about the study’s nature, purpose, and possible risks and benefits are given to the participants, confirming that they understand the study requirements according to the local ethics committee that approved the study (Process No. 10937419.0.0000.5404).

## Results

### Module 1

The development of module 1 has been completed, and the results are described in the following sections.

Recruitment began on October 1, 2021. The trial will complete the recruitment phase in June 2022, and the follow-up phase will end in August 2022. The publication of results is anticipated in 2023.

All steps of stage 1 (understanding unhealthy salt intake) have been entirely detailed.

### Step 1 of Stage 1: Definition of the Problem in Terms of Behavior (Unhealthy Salt Intake)

Due to the high salt consumption evidenced in the previous study in the same town where this project will be developed and considering the health risks and harms resulting from this consumption, there was a need to promote the healthy consumption of this nutrient not only to specific groups but also at the population level.

### Step 2 of Stage 1: Selection of the Target Behavior

Perin et al’s [8] study also demonstrated that, regarding the sources of salt intake, 24% came from the intrinsic sodium assessed from a 24-hour dietary recall and 7.3% from ultra-processed foods with high sodium content, and the addition of salt in food preparation was the behavior that contributed to 59.1% of the overall salt intake in the population. Thus, reducing salt addition in food preparation was selected as the target behavior of the intervention.

### Step 3 of Stage 1: Specification of the Target Behavior

In this step, it is essential to have a specific behavior because, according to Michie and collaborators [20], the clearer the behavior, the better your behavioral analysis. Thus, the salt added to food preparation will be monitored daily at home by the person or by the person helping them cook.

### Step 4 of Stage 1: Identification of What Needs to Change (the TDF and COM-B Model)

First, we selected the TDF using the determinants described in Cornélio et al’s [46] study. This study applied an extended version of the Theory of Planned Behavior among Brazilian individuals with hypertension and found that self-efficacy and habit were significant determinants of intention, explaining 62% of the variability of intention to add less than 4 g of salt per day in food preparation, and the intention, on the other hand, explained 22% of the variability of this behavior [46]. Thereby, the domains of the TDF were mapped from these three determinants—intention, self-efficacy, and habit—to identify what needed to change. In the second process, we identified the components of the COM-B model from the TDF domains, which could be physical capability, psychological capability, social opportunity, physical opportunity, reflective motivation, and automatic motivation. The findings are described in Table 1.

From this process, we are capable of developing stage 2: identifying intervention options.

**Table 1 table1:** Linking of the determinant of the TPB^a^, the domain of the TDF^b^, and the COM-B^c^ model based on Michie and collaborators [20].

Determinant of TPB (based on Cornélio et al [46])	Domain of TDF (definition)	Component of COM-B (definition)
Intention	Intentions (a conscious decision to perform a behavior or a resolve to act in a certain way)	Reflective motivation (reflective processes involving plans [self-conscious intentions] and evaluations [beliefs about what is good and bad])
Self-efficacy	Beliefs about capabilities (acceptance of the truth, reality, or validity about an ability, talent, or facility that a person can put to constructive use)	Reflective motivation
Habit	Behavioral regulation (anything aimed at managing or changing objectively observed or measured actions)	Psychological capability (knowledge or psychological skills, strength, or stamina to engage in the necessary mental process)

^a^TPB: theory of planned behavior.

^b^TDF: Theoretical Domains Framework.

^c^COM-B: Capability, Opportunity, Motivation, and Behaviour.

### Step 1 of Stage 2: Intervention Functions

The intervention functions that met the APEASE criteria were education (increasing knowledge or understanding), persuasion (using communication to induce positive or negative feelings, or to stimulate action), incentivization (creating an expectation of reward), modeling (providing an example for people to aspire to or imitate), enablement (increasing means or reducing barriers to increase capability or opportunity), and training (imparting skills).

Finally, after identifying intervention functions, we achieved stage 3: identifying content and implementation options.

### Step 1 of Stage 3: Behavior Change Techniques

The selection process of the techniques resulted in 31 BCTs after removing duplicates. In conclusion, after applying APEASE criteria, we had a list of 16 BCTs: goal setting (behavior), problem solving, goal setting (outcome), action planning, commitment, feedback on behavior, self-monitoring of behavior, social support (unspecified), social support (practical), instruction on how to perform the behavior, information about health consequences, demonstration of the behavior, prompt/cues, behavioral practice/rehearsal, credible source, and adding objects to the environment.

## Discussion

### Expected Findings

We have described our innovative protocol for an intervention to promote healthy salt intake using the BCW, a guide to designing behavior change interventions. The design of this protocol study has considered the evidence on the efficacy of changing eating behaviors using the BCW [19], the advances in the use of the technology of mobile apps in various areas of health (mainly in eating behaviors [47]), and the dietary recommendations to reduce salt intake for the prevention of cardiovascular diseases [48].

To our knowledge, there is only one study available in the literature that evaluated the effect of an app intervention to reduce salt consumption using BCW; however, the study was focused on people with arterial hypertension and not on the general population [49].

We expected that this theory- and evidence-based mobile app intervention would effectively promote healthy salt intake when cooking at home since this behavior is the primary source of consumption of this nutrient among the Brazilian population. We also hope that mobile apps as the mode of delivering the intervention will encourage and facilitate people’s self-care and work as an alternative or supportive method in the relationship between health care professionals and patients. Finally, it is expected that the study will inform the potential scalability and transferability of this intervention for achieving a broader public health impact.

The next phase of this research is to complete the development of module 2, the semistructured interviews with the potential users of the mobile app, and the mobile app. After that, we will implement and evaluate the intervention (module 3) using a randomized controlled study.

The results of this study will be published in peer-reviewed scientific journals and presented at scientific events in the thematic area. They will also be communicated to research participants and the public involved in the study through face-to-face presentations at the health services participating in the research.

